#### To test and compare both implementation strategies in terms of experiences of participants (process evaluation)

##### Study population

For the process evaluation, a sample of adult patients (*N* = 50; 5 per hospital) and healthcare professionals involved in their cancer care (*N* = 40; 4 per hospital) will be included. The patients included are again adult patients, diagnosed with cancer in the abdominal or pelvic cavity (ea. gastrointestinal, reproductive and urological system).

##### Data collection

In order to study the use of and experiences with the different elements of the implementation strategies and the modified care, a process evaluation will be performed. This will include the extent to which patients and professionals (when the strategy includes patient- and professional- directed elements) used the elements of the strategies and their experiences (e.g. satisfaction and feasibility) with these elements and the modified care. Process information will be gathered in a qualitative study in the 10 hospitals, in which the implementation strategies were tested. Individual interviews will take place among the patients and hospital professionals. For example, if a website for cancer patients with information about the importance of physical exercise is part of the strategy, patients are asked about the frequency they visited this website, their satisfaction with this website and how feasible it is to use the website. All interviews will be recorded and typed in a document.

##### Study outcomes

The use of and experiences with the elements of the strategies and the modified care by patients and professionals will be studied (both participation in and satisfaction with the different elements).

##### Planned analytic approach

For the process evaluation, interviews with professionals and adult cancer patients will be qualitatively analysed, using the qualitative software package Atlas.ti version 7. The process analysis will be descriptive. The descriptive outcomes of the PD- and MF-strategy group will be compared.

#### To test and compare both implementation strategies in terms of costs

To determine the cost and benefits per patient of the implementation strategies and their consequences, we will use an activity-based costing (ABC) approach [106]. ABC was developed by Robert S. Kaplan in the mid-1980s [107]. Academic researchers and accounting practitioners believe it is the most modern normative appropriate costing system that can properly and confidently give information for decision-making. ABC helps to get a more realistic view of the indirect costs by using multiple cost drivers. In ABC, the indirect cost is assigned to activities and products (healthcare services), via a cause and effect relationship. Healthcare systems are considered as an entity that includes series of activities for the purpose of performing healthcare services to the patients. These activities in a healthcare system generate costs, which include direct and indirect costs, but also benefits. Next to accurate cost information, ABC also provides a clear view of the activities in the healthcare services that might be used for evaluating healthcare process performances.

##### Study population

For the cost evaluation, the 10 hospitals of our study, their patients and professionals will be included. For the outline of the patient care processes, we will use a sample of 500 patients (about 50 adult patients per hospital). The characteristics of the patients will be the same as the characteristics of the study group of the ‘Analysis of the currently achieved implementation of PCRPs in daily care’ section. The meetings with professionals from the participating hospitals to reach a consensus on the protocol of processes (activities) of the PD and MF strategies will consist of 20 professionals, 10 professionals per cluster. All professionals should be involved in the treatment of cancer patients and the implementation processes of the PCRPs.

##### Data collection and planned analytic approach

By an ABC approach, we will try to calculate the actual costs and benefits for using the PD- and MF-implementation strategies. In order to accurately assign the costs to the implementation strategies and followed healthcare services, it is necessary to determine exactly the consumption of activities. Afterwards, we need to assign the costs of resources needed to deliver these activities.

The activities and the followed costs of resources (personnel, material and amortization of investment costs) to implement the PCRPs via the PD- or MF-implementation strategies are perceived as the costs, according to ABC approach. On other hand, the prevented activities and their costs of resources that are not used due the implementation of the PCRPs by the PD- or MF-implementation strategies are considered as the benefits. The costs will be measured from the time of preparation and development of strategies until 1 year after the start of the implementation strategies.

Our first step will be to develop protocols of activities performed during the (1) preparation and development of the strategies and (2) activities accumulated by the activity of the healthcare implementation processes (processes of care of patients involved in the implementation processes).

To determine the activities, we will select a sample of patients involved in the implementation process and outline the patient care processes (activities) in each case.

During meetings with professionals from the participating hospitals, we will try to reach a consensus on the protocol of processes (activities) of the PD and MF strategies. The protocol of processes will outline a description of processes and details of their constituent activities.

Our next step will be to proceed the allocation of resources used in each process. For collecting information on the use of the different elements of the implementation plan by professionals and patients, existing databases will be used as much as possible. When necessary, registration forms will be developed and will be completed by the professionals and the sample of patients involved in the implementation process. The input of resources in the implementation strategy will be assessed by collecting volumes of use of the different elements of the implementation strategy by professionals and patients and multiplying these by the price of each element (market prices, guideline prices or self-determined prices based on costing methods, i.e. full costing). Future costs and effects will be discounted at 4 and 1.5 %, respectively, according to the Dutch guidelines [108].

Cost prices of the processes will be determined using standard unit cost prices according to the Dutch guidelines for costing research [108]. If certain standard unit cost prices are not available, real cost prices will be determined by consulting the management of participating hospitals.

With the protocol of processes of activities and their cost of resources, we will calculate the incremental costs of both the PD and MF strategies. We will also calculate an incremental cost-effectiveness ratio (ICER). The outcomes used for calculating the ICER are the primary outcome measures of our effectiveness study (the ‘To test and compare both implementation strategies in terms of effectiveness’ section): (1) percentage of screened patients and (2) percentage of referrals to PCRPs were needed.

After this, we will compare the expected incremental cost (and potential savings) and cost-effectiveness ratios of the PD with the MF strategy.

##### Study outcomes

The expected costs (and potential savings) and ICERs of the development and use of the PD and MF strategies. Additionally, we will compare the outcomes of the PD strategy with the MF strategy.

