However, strategies aimed at professionals (educational outreach, audit and feedback) can also result in successful implementation (professional performance, patient outcomes and costs) [86, 87]. Strategies directed on the organization could support the implementation of PCRPs as well, mainly because contextual factors, such as workload, poor coordination and management, can be important barriers for success.

In our present study, we aim to identify the most effective strategy to implement PCRPs into daily care. Specific goals are to (1) gain insight into the specific features needed for a successful implementation by exploring the setting and factors (barriers and facilitators) that might influence the implementation of PCRPs. After this, (2) we aim to develop a patient-directed strategy and a multi-faceted strategy. The patient-directed strategy will be designed to embed the success of implementation of PCRPs by influencing the patients, and the multi-faceted strategy will be designed to embed the success by not only influencing the patients but also professionals and organizational aspects. Both strategies will be designed tailored to the setting and found factors affecting implementation. We also aim to (3) compare the effectiveness, experiences of participants (process evaluation) and costs of both strategies on the hospital and patient level and (4) get insight into the additional effects of strategies directed also at professionals and organization aspects compared to patient-only strategies.

Our first hypothesis is that hospitals with a multi-faceted strategy will have a more effective implementation of PCRPs in comparison with hospitals with a patient-directed strategy.

Our second hypothesis is that the patients and professionals will experience more positive experiences with the multi-faceted strategy in comparison with hospitals with a patient-directed strategy.

Our third hypothesis is that those hospitals with the multi-faceted strategy will have higher costs (incremental costs) in comparison with hospitals using the patient-directed strategy.

Our last hypothesis is that the incremental cost-effectiveness ratio (ICER) of the multi-faceted strategy will be lower than the patient-directed strategy.

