The results of the literature search will, together with the knowledge based on the results of the preparatory phase in step 1, be the basis to select and develop the implementation strategies during roundtable discussions. For the five hospitals of the PD-strategy group, a single-faceted patient-directed strategy will be designed that will embed the change only at the patient level. For the hospitals of the MF-strategy group, a multi-faceted strategy will be designed that will embed the change at the patient, professional and organizational levels. The MF strategy will consist also of the PD strategy, so the additional value of the strategies directed at the professional and organization can be evaluated afterwards. For the roundtable discussions, an expert panel will be composed consisting of representatives from the participating hospitals (patients, healthcare professionals and hospital managers), experts on cancer rehabilitation and experts on implementation science.

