## Conclusion

Our study is intended to highlight the important role of the right implementation strategy to provide evidence-based PCRPs to the patients. We believe that strategies tailored to the current setting and barriers and facilitators found will optimize the success of implementation of PCRPs. If one or both implementation strategies prove to be effective, the knowledge about the effectiveness, feasibility and cost of the tailored implementation strategies can help to apply these PCRPs successfully in the Dutch and other healthcare systems. Additionally, our study might give insight in the additional effects of strategies directed at patients, professionals and organizations in an implementation strategy for PCRPs. Finally, if the implementation strategies are effective, this will lead to improved survivorship care leading to better quality of life for cancer survivors.

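### Jointly incurred development cost enters both ICERs with no stated split, and comparing two separate ratios makes the last hypothesis depend on that split

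*Protocol article*

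**What the plan says.** Four parts of the protocol article bear on this.

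- **What is costed.** In the cost part of Step 3, Data collection and planned analytic approach: "The costs will be measured from the time of preparation and development of strategies until 1 year after the start of the implementation strategies". The Study outcomes paragraph there names the "ICERs of the development and use of the PD and MF strategies". The Abstract lists incremental costs and ICERs among the main outcome measures.
- **What is compared.** The last hypothesis in the Background is that "the incremental cost-effectiveness ratio (ICER) of the multi-faceted strategy will be lower than the patient-directed strategy". The costing section plans to "compare the expected incremental cost (and potential savings) and cost-effectiveness ratios of the PD with the MF strategy". Both wordings set one ratio beside another.
- **What is joint.** Under Step 2, the findings of the literature search and of step 1 will together "be the basis to select and develop the implementation strategies during roundtable discussions". One search, one preparatory phase and one series of discussions therefore serve both strategies. In addition, "The MF strategy will consist also of the PD strategy".
- **What is not joint.** For the MF hospitals, "a multi-faceted strategy will be designed that will embed the change at the patient, professional and organizational levels". The professional and organizational parts have no counterpart in PD.

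Indirect cost is to be assigned by cause and effect under activity-based costing, and investment costs are to be amortized. The article gives neither a rule for dividing the joint development cost nor an amortization period, and it gives no cost amounts.

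**The concern.** A cost that both strategies cause equally carries no information about which of them to choose. In a comparison of two separate cost-effectiveness ratios it still does not drop out. Each ratio takes on that cost divided by its own effect, so the ratio with the larger effect rises less. MF is the strategy expected to have the larger effect, so an equal charge pushes towards the hypothesised result.

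At stake is the verdict on the last hypothesis. Under some cost patterns it would turn on how the study's own preparatory spending is booked and not on what the strategies cost to use. The Conclusion says the knowledge gained "can help to apply these PCRPs successfully in the Dutch and other healthcare systems". Hospitals reading it that way need to see which part of the cost they would themselves face.

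**Working it through.** **Inputs.** The effects are the 50 % (MF) and 20 % (PD) of the Power calculation, taken here as gains in percentage points. The article does not say whether they are gains or levels. Group sizes are equal (five hospitals of 50 patients each), so an equal total charge is also an equal charge per patient, whether the joint cost is booked in full to each group or halved. All costs below are assumed, because the article states none. I take each strategy's ratio as its cost per patient over its own gain.

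**Notation.** c = cost of use, e = gain, D = joint development cost charged equally to both.

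ICER = (D + c) / e

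**Step 1: the push.** D adds D/20 to the PD ratio and D/50 to the MF ratio. The difference is D × (0.05 − 0.02) = 0.03 × D in favour of MF.

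**Step 2: when the verdict reverses.** Two conditions are needed:

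1. cMF/cPD > eMF/ePD (here 2.5). Otherwise MF already has the lower or equal ratio without development cost.
2. D > (cMF × ePD − cPD × eMF) / (eMF − ePD).

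Example with cPD = 100 and cMF = 300: the threshold is (300 × 20 − 100 × 50)/30 = 33.3.

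| D | PD ratio | MF ratio | Direct ratio, MF versus PD |
|---|---|---|---|
| 0 | 100/20 = 5.0 | 300/50 = 6.0 | 200/30 = 6.67 |
| 50 | 150/20 = 7.5 | 350/50 = 7.0 | 200/30 = 6.67 |
| 100 | 200/20 = 10.0 | 400/50 = 8.0 | 200/30 = 6.67 |

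The hypothesis fails at D = 0 and is met at D = 50 and D = 100. The direct ratio does not move.

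**Step 3: range over the use-cost ratio.** With r = cMF/cPD, the threshold in multiples of PD use cost is (20r − 50)/30:

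- r = 2: negative, so MF is already lower and nothing reverses
- r = 2.5: 0 (ratios equal without development cost)
- r = 3: 0.33
- r = 4: 1.00
- r = 5: 1.67

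**Step 4: range over the effects.** If 50 % and 20 % are levels over an assumed 10 % baseline, the gains are 40 and 10, and a reversal needs r above 4. Over an assumed 15 % baseline they are 35 and 5, and it needs r above 7.

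**Step 5: unequal charges.** Let MF carry share s of total development cost T. PD gains T(1 − s)/20 and MF gains Ts/50. These are equal when 50(1 − s) = 20s, so s = 50/70 = 71.4 %. With T = 200:

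- s = 50 %: 5.0 added to PD, 2.0 to MF (favours MF)
- s = 60 %: 4.0 and 2.4 (favours MF)
- s = 80 %: 2.0 and 3.2 (favours PD)

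Put differently, MF-only development cost above 1.5 times the joint charge turns the total effect of development cost against MF: (D + 1.5D)/50 = D/20.

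**The case against.** The best defence is that nothing in the article says the same amount goes to each strategy. Activity-based costing assigns cost by cause, and MF has professional and organizational elements that only MF causes. Step 5 shows that this can cancel or reverse the push. Amortization means that a full one-off charge is not established either. All of this stands. It does not settle the matter, because cause and effect cannot separate a cost that both strategies cause, and amortization shrinks D without removing the asymmetry.

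It can also be said that including development is a legitimate costing perspective, openly labelled, and that the costing section already plans separate activity protocols for development and for implementation. That is right: inclusion is not an error. The weak point is the comparison of two ratios with the split left open.

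Three stronger readings are tempting and are not supported:

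- *Shared development cost decides for MF whatever MF costs to run.* The threshold contains cMF. With cMF = 500 and cPD = 100, D = 100 gives 200/20 = 10.0 for PD and 600/50 = 12.0 for MF, with no reversal.
- *Later adopters would pay none of the development cost.* The Background and Conclusion both stress tailoring to the setting and its barriers, so an adopting hospital may well bear preparation costs of its own.
- *Taking development cost out of both ratios cures the problem.* The patient-directed elements also have a cost of use, which enters both numerators and acts in the same way. Only the direct ratio removes an equal common amount.

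**Conclusion.** The point holds as a matter of how the comparison is fixed. Development cost enters both ICERs, part of it is joint, its split is not stated, and the last hypothesis is judged on two separate ratios that are sensitive to that split. To the extent that the joint part is charged equally, the push is towards the more effective strategy, by 0.03 × D at gains of 50 and 20 points. MF-only development pushes the other way, and the two balance when MF carries about 71 % of the total.

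A reversed verdict needs both conditions in step 2. As the article gives no costs, and does not say whether 50 % and 20 % are gains or levels, a reversal is possible but not demonstrated. Nor can the net direction of the push be known in advance.

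**What to change.** In the cost part of Step 3:

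1. Record cost in separate layers: development (joint and MF-only apart), introduction per hospital, and running cost.
2. State how joint development cost is split between the strategies.
3. Report the ICERs with and without development cost.
4. Base the MF-versus-PD conclusion on the direct ratio, (cost MF − cost PD)/(effect MF − effect PD), in which an equally charged shared cost cancels. MF-only development does not cancel there and would show as part of the extra cost of MF. Reword the last hypothesis to match.

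The price is an extra column and a scenario in the cost table. The headline comparison would also no longer reflect the study's full development spending, which would be shown beside it. According to Trial status, no indicator data had been gathered and no analysis had begun, so the change can be made before any result is known.

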### Trial status

At the time of manuscript submission, the study is ongoing at step 1, the preparatory phase. Some interviews for examination of the factors (barriers and facilitators) for successful implementation of PCRPs have been performed, but no data analysis has begun.

Data on quality indicators, to analyse the actual performance of the current implementation of PCRPs in daily care, have not been gathered.

## Discussion

This is one of the few studies to develop and test two implementation strategies to implement PCRPs into daily healthcare in a structured and stepwise approach. In previous papers, PCRPs were implemented in German, United Kingdom, Canadian and American healthcare systems [62, 64–67]. To our knowledge, a study on the effectiveness and feasibility of implementation of PCRPs in a stepwise structured approach and performed on a large scale in the Dutch healthcare system has not been conducted before. The originality of our study is further supported by being one of the few that compares the effect of a multi-faceted strategy with a patient-directed strategy.

During the process of selecting strategies, it is important that the strategies will be evidence based and tailored to the barriers and facilitators that are directed on patients and in the MF-strategy group additionally also on professionals and the organization level. It is best to arrive to a cost-effective mix of measures and activities, which has preferably been found to be effective in similar situations [77].

Multi-faceted strategies targeting different barriers in different fields (patient, professional and organization) are more likely to be effective than single ones [71]. Therefore, it is more likely that our MF strategy, focusing also at professionals and the organization, will be more effective than the strategy that only embeds the change on the level of the patient. In most studies, the implementation of PCRPs is mainly supported by strategies directed at patients. Patient strategies, like empowerment-enhancing tools, are promising since they fit the patient-centred care approach and stimulate an active patient role and have the potential to improve the rehabilitation process itself [109, 110]. Enhancing empowerment has shown its clinical effect in the rehabilitation of patients with osteoporosis [111], hip fracture [112], and might also have its effect on the success of implementing PCRPs. Promising strategies directed at professionals are mainly active strategies, including educational outreach visits, reminders and audit. And a promising strategy directed at organizations is enhancing professional roles, healthcare pathways and mainly tools in an ICT format [86]. Experts conclude that further research is required to discover which strategies to present to target the different barriers and settings [71, 79].

With regard to the implementation of PCRPs, it is possible that strategies in an ICT format can contribute to the effectiveness of the implementation [96, 98, 113]. Implementation experts consider ICT to be the key to improve efficiency and quality of healthcare [114]. In our opinion, ICT can be effective at the level of the professionals or the healthcare teams to improve adherence to the programmes by clinical decision support systems, surveillance and monitoring. At the level of the patients, it can realize new forms of healthcare services outside the healthcare institutions and in the patient’s environment instead. It can also increase the level of patient empowerment by giving the opportunity to get insight in his/her medical data and become more involved in the rehabilitation process [115]. Additionally, ICT may also support the physical rehabilitation process by restoring health and improving outcomes, since previous studies have shown that ICT interventions may lead to improved physical activity levels, with promising outcomes in several patient groups [96, 116–119]. ICT tools and tools to enhance patient empowerment, designed and piloted by other A-CaRe research groups, will be incorporated in our implementation strategies.

Healthcare improvement programmes are well-known to be better adopted by socio-economically advantaged individuals as compared to disadvantaged individuals [120, 121]. Moreover, younger individuals are able to use and access ICT innovations easier than older individuals [122]. The design of our strategies will be developed with a pragmatic attitude [123, 124] to avoid increasing health inequalities by providing equal access to the PCRPs. Patients will not be selected on their exercise ability or history, and criteria are not restrictive to a particular population to fit with real clinical context. Nevertheless, we will focus on adult patient populations and will not include non-adult populations because of the differences in medical decision-making regarding children and adolescents, including the parent/guardian role and the different tumour types.

An important limitation of our study is the absence of a proper randomized study design. This would eliminate bias in implementation strategy assignment and improve the evidence that differences in outcomes between the implementation strategies indicate significant effects on physical cancer rehabilitation care [125]. It is, however, also known that comparing complex interventions and programmes is a challenging matter, for which one has to settle with less advanced designs.

Our implementation strategies have the disadvantage of measuring the effect of the entire package of interventions, which might make it hard to distinguish which intervention was most effective regarding improved cancer rehabilitation care (with indicator adherence as effect measure). During the evaluation, we will try to get insight into the effect of each separate intervention by acquiring information from participants concerning the exposure to, use of and experiences with the different interventions.

A dilution of treatment effect could occur if patients participate in a PCRP themselves or when professionals and organizations use their own implementation strategies to achieve proper implementation. Local initiatives to optimize cancer rehabilitation during the intervention period might bias our study results. Therefore, information on local, non-study-related interventions will be additionally acquired during the process evaluation.

Hospitals, which agree to participate in our study, are probably committed to improve their quality of cancer rehabilitation care and the implementation of PCRPs. Their results will be generalizable for hospitals motivated to implement PCRPs. For hospitals less committed to achieve this goal, the outcomes might be less generalizable.

